### Sample size

Sample size will be decided by the primary outcome. According to our unpublished pilot study and literature review [6], the proportions of patients with a more than 30% improvement in NAS scores in at least 2 out of 3 DPF items for acupuncture and placebo is 45% and 17.9% respectively. We use the proportion for placebo instead of the one in sham acupuncture group, because no data are available for sham acupuncture so far. A sample size of 52 for each group will be sufficient to detect a 2% null difference in proportion, with a two-sided 5% level of significance, and a power of 80%. The number of subjects is increased to 60 in each group (total of 120) when a drop-out rate of 15% is taken into consideration.

### Statistical analysis

For data analysis, statisticians and investigators will be blinded for the patients’ allocation. Statistical analysis will be performed using SPSS Ver.20 (SPSS Inc., Chicago, IL, USA) software. Enumeration data will be described as frequency and composition ratio. Continuous data will be presented by Mean ± Standard Deviation (M ± SD) if they meet normal distribution, otherwise they will be expressed as Medians ± Interquartile Range (M ± IQR). Categorical data will be presented by frequency and percentage. The analyses of efficacy will be based on the intention-to-treat (ITT) analysis set, which was defined as patients who receive at least one treatment. Missing data for the primary outcome will be treated by multiple imputation under chained equation, with m = 50 imputations. The covariates used to generate the multiple imputed data sets are age, sex, NAS scores of DPF, ESSDAI, ESSPRI, salivary flow rate, and Schirmer test score. For comparison with the baseline, a repeated measures data analysis of variance (ANOVA) or Wilcoxon signed rank test will be used for continuous data, whereas Chi-square test or Fisher exact test will be used for categorical data. In terms of comparison between the two groups, Chi-square test or Fisher exact test will be used for primary outcomes. For secondary outcomes, the analysis of covariance (ANCOVA) will be used if the residual are normal distributed, otherwise Wilcoxon rank sum test will be applied. To access the success of blinding, the proportion of subjects who are successfully blinded will be compared by Chi-square test or Fisher exact test. And nonparametric test will be used to analyze satisfaction. *P* <0.05 with two-tailed test indicates statistical significance.

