### Randomization and blinding

Subjects eligible for participation will be randomly assigned to one of the following study groups, using the randomization software SAS (Statistical Analysis System) 9.2.penetrating acupuncture: 60 subjectssham acupuncture: 60 subjects

The statisticians will randomize assignments using a sequence of number randomly generated by the SAS (Statistical Analysis System) 9.2, done by a third organization, a Statistical Department of State Standardized Traditional Chinese Medicine Pharmacology Clinic (SDSSTCMPC) granted by State Food and Drug Administration (SFDA). The sequence will be recorded and can be displayed when necessary. These assignments will be sent to a study member, who will put them into sealed, opaque envelopes with dates and signature labels over the seals. And this study member will not take part in any of patient interviews, acupuncture intervention, data collection, or statistical analysis.

Before eligible subjects are randomized into different groups, informed consent contract will be obtained from each participant and they will be interviewed to ensure their baseline data recorded. Then they will allocate and come to see the acupuncturist who will open the consecutive randomization envelope, and then apply acupuncture or sham one according to the assignment without informing the subjects of their assignments. As the only one knowing the group assignments of subjects, the acupuncturist will not participate in any of the interviewing, data collection, or statistical analysis. Every time before the intervention, except the first time, which is baseline, the subjects will come to the interviewing room where the case report form (CRF) with NAS scores will be filled with their feedback on NAS scores about last 24 h instead of a time point. After the intervention, the schedule for their acupuncture and interviewing for next time (including date and time) will be informed.

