### Limitations

Limitations include the restricted sample size and single centre. Although the study takes place in GAM hospital in Beijing, it is not possible to limit subjects into only local citizens as there is a large number of people immigrating to Beijing from all over China and so do the patients. Thus, the differences of people in different areas of China may interfere the outcomes of the trial. Although we only accept subjects having less than 5-year of symptomatic pSS, different durations of having it may also interfere the outcomes. Besides, we can’t eliminate the medicine interferences from those who are taking other medicines during the study. We don’t know what the informing strategy would actually and exactly bring to subjects mentally by telling them we are researching on a “new” method of acupuncture, although our initial purpose of doing so is to make subjects to have the same expectations from their interventions. Another limitation is that the acupuncturist knows assignments and he conducts, in which case the communication between the acupuncturist and subjects may, more or less, change the expectations of subjects, which would cause bias. What’s more, the acupoints studied in this trial are constant. It is not the way of applying acupuncture clinically in TCM way, in which case we wouldn’t know how acupuncture would act if it’s done with Differentiation Method, a way of diagnosis in TCM, which also directs treatments. Finally, if there is a third group by standard care, the result would be more convincing; while, standard treatments based on the guideline of pSS had not been established yet before the start of this study, and our fund is not financially supportive to set a third group of cohort.

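### The efficacy set labelled ITT is a treated-only set, so a randomised patient can leave it after the acupuncturist knows the arm

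*Protocol article*

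**What the plan says.** The Statistical analysis section of the protocol article places the efficacy analyses on "the intention-to-treat (ITT) analysis set, which was defined as patients who receive at least one treatment". It names no all-randomised set. For the primary outcome it adds: "Missing data for the primary outcome will be treated by multiple imputation under chained equation, with m = 50 imputations".

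Randomization and blinding gives the order of events. Before randomisation, patients consent and "they will be interviewed to ensure their baseline data recorded". They then "come to see the acupuncturist who will open the consecutive randomization envelope, and then apply acupuncture or sham one according to the assignment". This is done "without informing the subjects of their assignments". On the acupuncturist's role it says: "As the only one knowing the group assignments of subjects, the acupuncturist will not participate in any of the interviewing, data collection, or statistical analysis". The Limitations section of the Discussion returns to this role: "Another limitation is that the acupuncturist knows assignments and he conducts". The bias it has in mind there is communication that alters patients' expectations.

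**The concern.** Intention-to-treat means that everyone randomised is analysed in the arm assigned. A rule that also requires a first session makes membership depend on something that happens after randomisation. The result is a modified set carrying the ITT name.

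A treated-only set is usually easiest to accept when nobody involved in starting treatment knows the arm. That protection is incomplete here, because the one unblinded person opens the envelope and then delivers the session that admits the patient to the efficacy set. If a session were not given for a reason linked to both arm and prognosis, the comparison would no longer be fully protected by randomisation, and the result would still be called ITT.

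This is a stated definition, so it is not a detail that could simply be waiting in a separate analysis plan.

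**Working it through.** **Order of events** (Randomization and blinding)

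1. Consent and baseline interview.
2. The acupuncturist opens the next envelope, so one person now knows the arm.
3. The first real or sham session is given.
4. Under the Statistical analysis definition, the patient enters the efficacy set only at step 3.

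A patient who reaches step 2 but not step 3 is randomised, has baseline data, and is left out. Nothing elsewhere in the article brings that patient back. The planned imputation does not, because it serves a set that has already lost the patient.

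**Inputs for size** (Sample size section): 60 per arm; assumed response 45% with acupuncture and 17.9% with placebo; target difference 45 − 17.9 = 27.1 points. The number of untreated patients is not given, so the counts k below are assumptions.

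**Worst case, one arm only.** Of 60 acupuncture patients, 60 × 0.45 = 27 respond. Remove k patients, all non-responders, from that arm. The observed rate becomes 27/(60 − k).

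| k | Acupuncture rate | Shift, if true rate is 45% | Shift, if true rate is 17.9% |
|---|---|---|---|
| 1 | 27/59 = 45.8% | +0.8 points | +0.3 points |
| 2 | 27/58 = 46.6% | +1.6 points | +0.6 points |
| 3 | 27/57 = 47.4% | +2.4 points | +0.9 points |
| 5 | 27/55 = 49.1% | +4.1 points | +1.6 points |

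**Milder cases for k = 3.** If three non-responders are lost from each arm, both rates are multiplied by 60/57, and the difference goes from 27.1 to 27.1 × 60/57 = 28.5 points, a shift of 1.4. If the loss is unrelated to prognosis, the expected shift is zero.

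**False-positive chance in the same worst case.** With a true response of 17.9% in both arms, 60 randomised per arm, k non-responders removed from acupuncture only, and an uncorrected two-sided 5% chi-square test, the chance of a significant result favouring acupuncture (nominal 2.5%) is:

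| k | 0 | 1 | 2 | 3 | 5 |
|---|---|---|---|---|---|
| Chance | 2.4% | 2.8% | 3.2% | 3.4% | 4.4% |

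**Would imputation undo the k = 3 shift?** Put the three patients back and impute them:

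- At the observed acupuncture rate of 47.4%: (27 + 3 × 0.474)/60 = 47.4%, the same as leaving them out.
- At a rate pooled over arms: expected sham responders are 60 × 0.179 = 10.74, so the pooled rate is (27 + 10.74)/(57 + 60) = 32.3%, giving (27 + 3 × 0.323)/60 = 46.6%.
- Counted as non-responders: 27/60 = 45.0%.

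Both imputation rates are shown because the listed imputation covariates do not include arm. Only the non-responder rule returns 45.0%.

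**The case against.** The strongest reply is that the gap hardly ever opens. Envelope and first session appear to fall within one visit, envelopes are consecutive, and patients are not told their arm. Both arms are presented to them as penetrating needling, so a patient's own decision to leave before the first session should not depend on arm. This stands, and it is why the likely number is very small and possibly zero.

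A reader might infer that the unblinded acupuncturist decides who counts as treated, or that the definition breaks the randomised comparison. The documents do not support either reading. No section gives the acupuncturist discretion to withhold the first session. The acupuncturist treats according to the envelope, follows a standard operating procedure, and is kept out of interviewing, data collection and analysis. The Limitations section raises a different route to bias. One can imagine a contraindication, such as a skin lesion at an acupoint, being noticed only at the first needling and weighed differently for a penetrating needle than for a blunt one. That is inference from the exclusion criteria, not something the plan describes.

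The illustration is also extreme. Response rests on the average of weeks 2 to 8 against baseline, so nobody can know before the first needle who will fail to respond.

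Finally, the definition sits beside the label, so a careful reader of this article can see who is analysed. That limits the harm from the name. It does not make the set intention-to-treat, and a later report that only says ITT would lose the qualification.

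**Conclusion.** The point holds as a wrong definition with a small possible consequence. The set is treated-only and should not be called ITT, and the allocation sequence makes exclusion after the arm is known possible. That much rests on the text alone.

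Bias is possible but not shown. The 2.4-point shift (45.0% to 47.4%), against a target difference of 27.1 points, is a one-sided worst case. It assumes three untreated patients, all in the acupuncture arm and all non-responders, and imputation alone would leave most or all of it in place. Exclusions unrelated to prognosis would give no expected shift.

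The matter is still worth correcting, because it fixes a stated rule at almost no cost.

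**What to change.** In Statistical analysis, replace the definition of the set so that:

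- the primary efficacy set is all randomised patients, analysed in the arm assigned;
- missing primary outcomes, including those of untreated patients, are handled by the planned multiple imputation, using the baseline data recorded before randomisation;
- a sensitivity analysis counts untreated patients as non-responders, since imputation alone would not answer the worst case;
- patients with at least one treatment form a sensitivity set, labelled modified ITT;
- the number of randomised but untreated patients is reported by arm.

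The cost is a few sentences and one or two extra analyses. Very few patients, if any, are added, and all should have baseline data. The planned 60 per arm is unchanged.

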#### Primary outcome

The numeric analog scale (NAS) [14] scores of DPF (0 = the best, 10 = the severest) will be measured at the baseline, three times a week in week 1 to 8, and once a week in week 12, 16, 20, and 24. By the comparison of the average scores of week 2 to 8 with those of the baseline of the two arms, the proportions of the subjects in two groups that have 30% or greater reductions in NAS scores in at least 2 out of 3 DPF items, will be the primary outcome.

Subjects will be asked to provide every NAS score based on the overall situation of the past 24 h [15] rather than a point of time. And we will collect NAS scores 3 times a week in week 1 to 8 (24 times in total).

The mentioned outcome measurements will be assessed at the marked time points respectively (Fig. 3).

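### The imputation rule most naturally fills in the yes/no responder status rather than the NAS scores behind it, and its covariate list omits arm; imputing the scores within arm would be safer

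*Protocol article*

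**What the plan says.** The Primary outcome section defines the outcome as "the proportions of the subjects in two groups that have 30% or greater reductions in NAS scores in at least 2 out of 3" of the symptom items. It is obtained as follows: "By the comparison of the average scores of week 2 to 8 with those of the baseline of the two arms". On data collection it says "we will collect NAS scores 3 times a week in week 1 to 8 (24 times in total"). The outcome is thus a yes/no status per subject, computed from three item averages.

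On missing data, the Statistical analysis section says: "Missing data for the primary outcome will be treated by multiple imputation under chained equation, with m = 50 imputations". It continues: "The covariates used to generate the multiple imputed data sets are age, sex, NAS scores of DPF, ESSDAI, ESSPRI, salivary flow rate", and the Schirmer score completes the list. Treatment arm is not on it. The section does not say whether the status or the scores are imputed, or which NAS time points enter. The Fig. 3 legend labels the first outcome simply as the NAS for dryness, pain and fatigue.

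**The concern.** The sentence names the primary outcome as the thing imputed and NAS scores as covariates. Read with the outcome definition, this makes the derived status the imputed variable and the scores its predictors. Each way of filling in the unstated time points then has a weakness.

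- **Baseline scores only.** The other clinical covariates (ESSDAI, ESSPRI, salivary flow, Schirmer) are scheduled at baseline and weeks 8, 16 and 24, so for anyone who leaves before week 8 they exist only at baseline. If NAS is also baseline only, nothing observed on treatment informs the imputation. A patient who leaves because nothing improved is given the response of completers who started at the same level.
- **All weekly scores.** The status is a deterministic function of baseline and the week 2 to 8 scores. A logistic model with that many score predictors and about 100 completers can classify them perfectly and then has no finite fit.

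Leaving arm out of a model for the outcome also pulls the imputed response rates of the two arms together. At stake are the size of the treatment difference and the use of information already collected.

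**Working it through.** **Inputs from the protocol article.** Response rates: "for acupuncture and placebo is 45% and 17.9% respectively", a difference of 27.1 points. Drop-out 15%, with no split by arm, timing or reason. 60 per arm. 50 imputations. Score SDs, correlations and the drop-out mechanism are not in the document, so all simulation inputs for these are assumptions.

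**The plan's own figure.** No figure for imputation error is stated. The sample size that supplies the yardstick does reproduce. With a null difference of 0.02 the distance is 0.271 − 0.02 = 0.251, and the mean rate is 0.3145. Then n = [1.960·√(2·0.3145·0.6855) + 0.842·√(0.45·0.55 + 0.179·0.821)]² / 0.251² ≈ 52.3 per arm, against the stated 52.

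**Readings at stake.** Weeks 2 to 8 give 7 × 3 = 21 readings per item. A patient who leaves after week 5 has given 4 × 3 = 12 of them.

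**Limits by arithmetic, status imputed at the completers' rate in the same arm.** If every drop-out is a non-responder, a true rate p becomes p/(1 − d).
- Acupuncture only, d = 15%: 45/0.85 − 45 = +7.9 points on the difference.
- Sham only, d = 15%: 17.9/0.85 − 17.9 = 3.2, so −3.2 on the difference.
- Both arms: 7.9 − 3.2 ≈ +4.8.

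**Arm omitted, drop-out at random.** If drop-outs in both arms get one common rate, the difference shrinks by about 0.15 × 27.1 = 4.1 points.

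**Large-sample simulation** (40,000 per arm, three items, eight weekly scores, true difference about 27 points, drop-out depending on the last observed scores). The first two rows are at 15% average drop-out; the last two also include a 30% case.

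| Imputation | Bias of the difference, points |
|---|---|
| Status from baseline NAS, with arm | +0.2 at random; −2.7 to +3.3 when related to response |
| Status from baseline NAS, arm omitted | −3.7 at random; −1.2 to −6.5 otherwise; six of nine cases between −3.7 and −4.9 |
| Status from observed weekly scores | within 0.3 with arm; −0.2 to −0.8 without |
| Scores imputed, then status derived | −0.3 to +0.1 with arm; −0.3 to −0.8 without |

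At 30% drop-out, status imputation from baseline NAS with arm gave +4.3, but that is twice the planned rate.

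**Lack of benefit driving drop-out in one arm only** (status from baseline NAS, arm in the model; two separate simulations).
- Acupuncture only, 15%: +2.7 to +5.7 and +4.3 to +5.9.
- Sham only: −1.5 to −2.7 at 15%, and −2.4 to −3.1 at 15 to 20%.
- Both arms, with drop-out of 13% and 21%: the arm rates were overstated by 3.6 and 3.2 points, so the difference moved by only 0.4.

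**Separation at the trial's size.** 85% of 120 is 102 completers. With baseline plus 3 × 8 = 24 weekly item means as predictors, the logistic model separated completely in 99.5% of 200 simulated trials in one run and in every trial of another. With raw readings there would be 3 × 24 = 72 on-treatment scores.

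**The case against.** The strongest reply is that the plan never says the yes/no status is imputed. The Fig. 3 legend calls the NAS scores the first outcome, and the Primary outcome section opens with those scores. In chained equations each variable predicts the others, so a list containing the NAS scores is also what score-level imputation would look like. This stands: status imputation is the more natural reading, not a stated rule.

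A reader might go further and infer that a drop-out's on-treatment readings are discarded by design. The text does not support that. NAS scores are named as covariates and are not restricted to baseline. Nor does the text say that a partly observed average counts as missing. The readings go unused only under the baseline-only reading.

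It can also be said that status imputation with weekly scores as predictors was nearly unbiased. That was so at 40,000 per arm. With about 102 completers, an unpenalised logistic step cannot be fitted in the usual way, so that result does not carry over unless the model is reduced or penalised.

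Finally, this is a condensed article, and time points and rules for partial averages are commonly left to a SAP. Their absence alone is not a fault. But the article itself fixes the target, method, number of imputations and covariate list, and what it fixes can be improved.

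**Conclusion.** The point holds as a cheap improvement to a rule that is written loosely and leans the wrong way. It is not a demonstrated error in the trial's result.

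At the planned 15% drop-out, status imputation from baseline scores with arm in the model gives about 0 to 3 points of bias in most cases, in either direction. It reaches about +6 only if lack of benefit drives drop-out in the acupuncture arm alone. With arm omitted, as the list reads, the bias is mostly about −4 points. All of this is against a planned 27.1.

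A reader might infer a general bias of 4 to 6 points. The documents do not support that. Similar drop-out mechanisms in both arms largely cancel, and sham-only drop-out at 15% cannot exceed −3.2. A bias of −4 from sham alone needs 17.9/(1 − d) − 17.9 = 4, that is d ≈ 18%, with every sham drop-out a non-responder. The simulated sizes rest on assumed score distributions and drop-out mechanisms. The arithmetic limits rest only on the planned rates and 15%.

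**What to change.** State in the Statistical analysis section that the weekly mean NAS score of each item (dryness, pain, fatigue) is imputed by chained equations, separately within each arm. Use baseline and all observed weeks of the three items plus the covariates already listed. In each of the 50 data sets, compute the week 2 to 8 item means and then the responder status, and pool the results. This also settles how a partly observed week 2 to 8 average is handled and makes the NAS time points explicit.

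It needs no new data, only a change of wording and some extra programming. The downside is a larger imputation model: 3 baseline scores, 24 weekly means and the six other listed covariates make 33 variables for 60 patients per arm. Weekly means instead of raw readings keep this manageable.

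### The covariate list for imputing the primary outcome leaves out the randomised arm; followed as written, this pulls the treatment difference towards zero

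*Protocol article*

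**What the plan says.** Everything on this point is in the protocol article, mostly under Statistical analysis.

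- Method: "Missing data for the primary outcome will be treated by multiple imputation under chained equation, with m = 50 imputations".
- Imputation variables: "covariates used to generate the multiple imputed data sets are age, sex, NAS scores of DPF, ESSDAI, ESSPRI, salivary flow rate". The last entry on the list is the Schirmer result. The randomised arm is not named, separate imputation by arm is not mentioned, and no time points are given for the NAS, ESSDAI, ESSPRI, salivary or Schirmer values.
- Between-group comparison: "Chi-square test or Fisher exact test will be used for primary outcomes".
- Analysis set: the "intention-to-treat (ITT) analysis set, which was defined as patients who receive at least one treatment". A patient who leaves after one session therefore stays in the analysis and needs an imputed outcome.
- Planning rates, under Sample size: the responder proportion "for acupuncture and placebo is 45% and 17.9% respectively". The same section allows for 15% drop-out and plans 60 patients per group.

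**The concern.** An imputation model should contain the contrast that the analysis will estimate. If the arm is absent, missing outcomes are drawn as though acupuncture and sham patients with the same covariate values had the same outcome distribution. Observed patients then show the full arm difference, while imputed patients show only the part that passes through the listed covariates. The pooled difference is pulled towards zero, even when data are missing completely at random.

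At stake are the size of the primary treatment effect and the power to detect it. The article goes far enough to name the method, the number of imputations and the covariates, so this is more than a detail left to an unseen analysis plan.

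**Working it through.** **1. The plan's own figure.** Inputs from Sample size: p1 = 0.45, p2 = 0.179, two-sided 5%, power 80%, and "A sample size of 52 for each group will be sufficient to detect a 2% null difference in proportion". Take the detectable difference as 0.271 − 0.02 = 0.251 and the mean rate as (0.45 + 0.179)/2 = 0.3145:

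n = [1.96 × √(2 × 0.3145 × 0.6855) + 0.842 × √(0.45 × 0.55 + 0.179 × 0.821)]² / 0.251² = 52.3

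This agrees with the stated 52 per group, and 52 × 1.15 = 59.8 gives the planned 60. The sample size is not in dispute here; it supplies the rates and the 15%.

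**2. Worst case by arithmetic.** Suppose the covariates carry nothing about the treatment effect, the arm is omitted, and a fraction f is missing equally in both arms. Missing responses are then drawn at the pooled rate of 31.45%:

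- acupuncture: (1 − f) × 45% + f × 31.45%
- sham: (1 − f) × 17.9% + f × 31.45%
- difference: (1 − f) × 27.1 points

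| Missing | Expected difference (points) | Loss (points) |
|---|---|---|
| 0% | 27.1 | 0 |
| 5% | 25.7 | 1.4 |
| 10% | 24.4 | 2.7 |
| 15% | 23.0 (43.0% vs 19.9%) | 4.1 |
| 20% | 21.7 | 5.4 |

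**3. Simulation at 15% missing.** Assumptions: 60 per arm; three correlated DPF items; true responder rates 45% and 17.9%; outcomes missing completely at random; normal-model multiple imputation with 20 imputations; Rubin's rules; 1,500 trials per row. The Monte Carlo standard error of the difference is about 0.2 points.

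| Covariates in the imputation model | Arm omitted: difference, power | Arm included: difference, power |
|---|---|---|
| Baseline only | 23.1, 77% | 26.8, 86% |
| Plus on-treatment NAS, weakly tracking the outcome | 24.9, 84% | 27.5, 90% |
| Plus on-treatment NAS, closely tracking the outcome | 26.2, 89% | 26.9, 90% |

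A separate simulation of 3,000 trials gave 23.1 points and 78% power without the arm, and 26.9 points and 86% with it.

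Omitting the arm lowered the estimate in every row. The gap is 3.7 points with baseline covariates, about 2.6 with weakly tracking NAS and 0.7 with closely tracking NAS. The last two rows assume that some on-treatment NAS exists for every patient, so a patient who left after one session is better described by the first row.

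**4. How much will be missing?** The 15% covers a 24-week trial, whereas the primary outcome uses weeks 2 to 8. If drop-out were even over time (an assumption; the article gives no timing), about 15% × 8/24 = 5% would be lost by week 8. Drop-out concentrated early would bring the figure nearer 15%.

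**The case against.** The strongest reply is that the arm may not be omitted in practice. The article does not say that only these variables are used; the word covariates often means patient characteristics other than the randomised group; and a fuller plan may exist. This stands as far as it goes: the text does not prove that the arm will be left out. It does state the model, and a reader who follows it would leave the arm out.

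The second reply concerns size. A reader might infer that imputed patients are simply given one common response rate, so that the effect shrinks in direct proportion to the missing data. The article does not support that in general. The list includes NAS scores of the outcome's own three items, which are collected three times a week in weeks 1 to 8, and ESSPRI, which covers the same symptoms and is also measured after baseline. Neither is restricted to baseline values. To the extent that on-treatment values enter, they carry part of the arm effect.

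Third, shrinkage towards zero does not create a false positive for superiority. That also stands and lowers the severity. The Discussion does speak of showing acupuncture to be no worse than sham, a claim for which shrinkage is not protective in general, but the article defines no such analysis.

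Blinding of the statisticians is no reason to omit the arm, because a masked code is enough.

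**Conclusion.** The concern holds in a conditional form. The stated imputation list lacks the randomised arm, and following it biases the primary difference towards zero.

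- Baseline or uninformative covariates, 15% missing: about 23 points instead of 27.1, with power about 77-78% instead of about 86%.
- On-treatment NAS in the model, 15% missing: a loss of about 1 to 3 points, with simulated power still above 80%.
- Worst-case covariates, 5% missing: a loss of about 1.4 points.

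These figures rest on the planning rates, equal missingness in the two arms, and the simulation's assumed item distributions and correlations. The 15% is the trial's drop-out allowance, used here as an upper assumption for the week 2-8 outcome and not as a known missing rate.

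A reader might conclude that the trial will certainly fall below its planned 80% power. The article does not support that, because it depends on covariate time points and a missing fraction that are not given. This should be fixed before unblinding, but it does not undermine the design.

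**What to change.** Add one sentence to the Statistical analysis section or the analysis plan:

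- include the masked arm code (A/B) in the imputation model, or impute separately within each coded arm;
- keep the listed covariates and include the available on-treatment NAS scores for each of the three items, summarised if needed so that the model can be fitted with 120 patients;
- state the time point at which each covariate is taken.

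The cost is one line of text. It needs no extra patients or data, and the statisticians stay blinded because they see only the code.
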